**Anti-FMP010 antibody responses**

Anti-FMP010 antibody concentrations will be summarized by Geometric Mean Titers (GMTs), with the 95% CI, at each time point at which blood samples are taken for serology.

Peak responses (Day 70) will be compared by Student’s t test on data normalized by log transformation to ascertain presence or absence of significant dose response difference. An adjustment to the statistical method will be made if multiple comparisons are warranted

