# Background:

This is the second part of the protocol listed above. The study is being conducted in two parts at two different sites. Part A (the Phase 1a portion) is being conducted at the Walter Reed Army Institute of Research in the USA. Part B (The Phase 1b portion) is being conducted at the Walter Reed Project/Kenya Medical Research Institute in Kisumu, Kenya. This covers Part B which will be conducted in Kisumu, Kenya.

The vaccination groups in Part A will be called Group 1 and Group 2. For ease of identification, the vaccination groups in Part B will be called Group 3 and Group 4.

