Although MSP1-based vaccines such as the 3D7 allele have been tested previously in humans, this is the first time that this candidate antigen (FMP010) based upon the FVO allele will be administered in humans. Therefore, a dose-escalation approach (1/5th dose of 10 micrograms and a full dose of 50 micrograms) will be taken to evaluate safety and reactogenicity in healthy malaria-naïve individuals in the U.S. Safety will be assessed after the first 1/5th dose has been given prior to proceeding to the full dose. Safety of the full dose in adults in the U.S. will be assessed after two vaccinations prior to proceeding to administration of the full dose in malaria-experienced healthy adults in Western Kenya. The candidate vaccine, FMP010/AS01B, consists of the FMP010 antigen formulated with GSK proprietary adjuvant AS01B, the adjuvant currently considered for use in planned pediatric Phase 3 malaria vaccine trials with the pre-erythrocytic malaria candidate vaccine, RTS,S/ASO1B.

Prior experience with MSP1-based vaccines in humans has indicated the requirement for potent adjuvants to elicit sufficiently high antibody titers against epitopes within the carboxy-terminal region of MSP1. Pre-clinical immunogenicity studies in small animals indicate that the FVO allele of the MSP1 antigen is superior to the 3D7 allelic variant in producing functional anti-parasite antibody activity as assessed in the in vitro growth inhibition assay (GIA).

A previous Phase 1/2b pediatric malaria vaccine study conducted in Kenya with the 3D7 allele of MSP1 (FMP1) in the adjuvant AS02A did not adequately demonstrate protective efficacy against clinical disease (manuscript in preparation). However, the 3D7 allele is rare at this location. Most adults in the target study population already have some level of pre-existing immune response to this antigen, therefore data from this population will be required to make an accurate assessment of the immunogenicity of the vaccine.

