**Study design**

| **Part B: RANDOMIZED, BLINDED IN WESTERN KENYA** | | | | | | | |
| --- | --- | --- | --- | --- | --- | --- | --- |
| Group | Location | Study Design | Test Article | Volunteers per group | Dose 1 | Dose 2 | Dose 3 |
| 3 | USAMRU-K, Kenya | Controlled Double Blind | Full dose (50 mcg) of FMP010/AS01B | 20 | **Part B Day 0** | **Part B Day 28** | **Part B Day 56** |
| 4 | USAMRU-K, Kenya | Controlled Double Blind | Rabipur Rabies Vaccine | 10 | **Part B Day 0** | **Part B Day 28** | **Part B Day 56** |

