### Study Design

This trial will be conducted in two parts. Part A will be conducted in the US at WRAIR and Part B in at the Walter Reed Project/KEMRI in Kisumu, Kenya. A total of 56 volunteers will be enrolled with 26 enrolling in part A and 30 in part B. For Part B, 20 volunteers (minimum 16) will be enrolled to receive FMP010 at 50 µg in AS01B (Group 3) and 10 (minimum 8) volunteers enrolled to receive a comparator rabies vaccine Rabipur (Group 4). This part will be randomized and blinded.

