#### Precautions to Minimize Risk

As outlined above, the volunteers will be monitored closely during their participation in this study. The study vaccine has been prepared according to Good Manufacturing Practices (GMP). The vaccines will be administered under the supervision of an investigator and nurses equipped with drugs and equipment to immediately treat anaphylaxis.

The vaccine will be tested at 1/5th and full dose in healthy adults in the US, prior to any vaccinations in Kenya. Additionally, the data from the US will be reviewed by a data safety committee prior to any vaccinations in Kenya. Only the full dose (50 µg) of FMP010 will be administered in Kenya under part B of the protocol.

Phlebotomy will be done by aseptic technique by trained staff, to reduce the risk of complications.

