**Visit 2: Day 0 – Vaccination 1**

- Check/verify inclusion/exclusion criteria and contraindications/precautions
- History and history-directed physical examination and recording of pre-vaccination data including vital signs
- Collection of urine for -HCG pregnancy tests where applicable
- Blood collection:
  - **Part B (Kenya):** Approximately 11 mL whole venous blood will be collected:
    - 5 mL for a CBC, creatinine, AST and ALT
    - 5 mL for humoral immune studies (ELISA, GIA). The research samples will be centrifuged and the serum stored at ‑20°C (± 5°) or colder until processing.
    - 1 mL for *P. falciparum* antigens detection by HRP 2 and pLDH ELISAs

- Vaccination: IM administration of FMP010/AS01B candidate malaria vaccine(or Rabipur® vaccine for Part B)in the deltoid muscle of the non-dominant arm

NOTE: Each vaccinee will be closely observed for at least 30 minutes following vaccination. After observation, blood pressure (BP), pulse, oral temperature, and solicited and unsolicited symptoms will be reviewed. Volunteers will be instructed to contact the study team immediately should they manifest any signs or symptoms they perceive as serious.

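### The one stated ELISA test looks for a dose response that Part B cannot show and the ELISA objectives do not ask for, and it leaves out the Day 0 titre

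*Protocol*

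**What the plan says.** Section 10.4.3 of the protocol (Anti-FMP010 antibody responses) summarises titres as geometric means with 95% CI at every serology time point. It then specifies Student's t test on the Day 70 values, "on data normalized by log transformation to ascertain presence or absence of significant dose response difference". The only adjustment it mentions is a conditional one for multiple comparisons.

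The surrounding text fixes the setting:

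- Scope (Background): "This covers Part B which will be conducted in Kisumu, Kenya".
- Arms (Study design table): Group 3 receives "Full dose (50 mcg) of FMP010/AS01B" and Group 4 receives rabies vaccine. Precautions to Minimize Risk restricts the Kenyan part to the full dose: only that dose "of FMP010 will be administered in Kenya under part B of the protocol".
- Two dose levels, "1/5th dose of 10 micrograms and a full dose of 50 micrograms", appear in the Study Rationale for the US volunteers.
- Size (section 5.3, Study Design): "20 volunteers (minimum 16) will be enrolled to receive FMP010", with 10 controls (minimum 8).
- Population (Study Rationale): most adults "already have some level of pre-existing immune response to this antigen".
- Day 0 sampling (Visit 2): "5 mL for humoral immune studies (ELISA, GIA".
- ELISA objective: the synopsis asks only for measurement in Kenyan adults. Sections 2.1 and 10.1 ask for a comparison of Kenyan with US adults.

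**The concern.** A test needs a contrast, and the one named here does not exist in the part of the trial that this document governs. Whoever runs the analysis must either drop the test or choose the comparison after the fact: vaccine versus control, or Kenya versus US. These are different questions with different weaknesses.

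Whichever is chosen, the stated method uses Day 70 alone. In a population expected to carry prior antibody, part of the Day 70 titre was there before vaccination. The same section reads the growth inhibition assay against each volunteer's own pre-immune serum, so the protocol recognises the baseline issue for one assay and leaves it out of the test for the other. At stake is how clearly a 30-person trial can show what the vaccine added to ELISA antibody.

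**Working it through.** **1. Purpose against design and objectives.** FMP010 dose levels in Part B: one. Possible dose contrasts: none. The only within-part contrast is Group 3 versus Group 4. None of the three statements of the ELISA objective (synopsis, 2.1, 10.1) mentions dose response.

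**2. Figure to reproduce.** None. The sample size section says only, in words, that power is low except for very large differences. The protocol gives no SD, effect size or alpha. Two-sided alpha 0.05, 80% power, the log10 SD and the Day 0–Day 70 correlation (rho) are assumptions below.

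**3. Stated test applied to Group 3 versus Group 4.** The standard error of a mean difference is SD × √(1/20 + 1/10) = 0.387 SD. By noncentral t with 28 df, the difference detectable with 80% power is 1.12 SD. As a fold difference, 10^(1.124 × SD), that is 2.2, 3.7 or 6.1 at log10 SD 0.3, 0.5 or 0.7. At the minimum 16 versus 8 it is 1.27 SD. This agrees with the protocol's own statement about power. For a true 0.8 SD difference the noncentrality is 0.8/0.387 = 2.07, giving power of about 51%.

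**4. The same contrast adjusted for Day 0.** ANCOVA reduces the residual SD by √(1 − rho²). The detectable difference follows by multiplication, for example 1.124 × √(1 − 0.5²) = 0.97 SD. This closed form ignores the small losses from estimating the slope and from chance baseline imbalance. The power columns come from simulation at 20 versus 10, include those losses, and are approximate to a point or two.

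| Assumed rho | Detectable difference (SD) | Power for 0.8 SD, ordinary errors | Power for 0.8 SD, HC3 errors |
| --- | --- | --- | --- |
| no adjustment | 1.12 | 51% | – |
| 0.3 | 1.07 | 53% | 49% |
| 0.5 | 0.97 | 61% | 56% |
| 0.7 | 0.80 | 79% | 75% |
| 0.8 | 0.67 | 91% | 88% |

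**5. Chance imbalance at Day 0.** The difference in mean log titre between the randomised arms has standard error 0.387 SD, so a 95% range of ±1.96 × 0.387 = ±0.76 SD. At log10 SD 0.5 that is about 2.4-fold. A Day 70-only test carries whatever part of this persists to Day 70.

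**6. Kenya versus US.** On the log scale, the difference in mean Day 70 titre equals the difference in mean Day 0 titre plus the difference in mean rise. Randomisation makes the first term zero on average for Group 3 versus Group 4. Nothing does so for malaria-experienced versus malaria-naïve adults, and the protocol's rationale implies that it is not zero. A Day 70-only test cannot separate the two terms.

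**7. Unequal variances.** Simulated type I error of the pooled test at 20 versus 10 is about 8.5%, 11% and 14.5% if the control SD is 1.5, 2 or 3 times the vaccine SD, and about 2% if it is half. The Welch form stays near 5% throughout. The protocol gives no SDs and does not say which group is more variable.

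**The case against.** The phrase is most plausibly carried over from text shared with Part A, which does have two dose levels. The endpoint is tertiary, the protocol already warns of low power, and its stated progression criteria rest on growth inhibition, not ELISA. The synopsis objective of measuring titres is met by geometric means with confidence intervals. Covariates and the variance form of a t test are commonly left to a SAP, which is not at hand.

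Much of this stands and limits the weight of the point. It does not remove it. Section 10.4.3 of this Part B document does not confine the sentence to Part A. The protocol has not stayed silent on method: it fixes a Day 70 test with a purpose that its own design rules out. The sample size section also says that comparisons will be made.

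Three stronger readings are tempting, and the document does not support them:

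- *That Day 0 is ignored.* It is not: Day 0 titres appear in the descriptive geometric means, and only the test omits them.
- *That a Day 70 comparison of Group 3 with Group 4 is invalid or biased.* Randomisation protects it on average, and the cost is precision.
- *That the pooled t test inflates false positives.* That needs controls to be the more variable group, which the protocol does not state. The error could equally fall below 5%. If the vaccine had no effect on titre at all, both randomised arms would share one distribution and the test would hold its level.

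**Conclusion.** The point holds as a mismatch inside the protocol plus an avoidable loss of information. The mismatch rests on the text alone and needs no assumption. The gain from using Day 0 depends on the assumed correlation: for a 0.8 SD difference at 20 versus 10, about 10 to 40 percentage points of power with ordinary errors at rho 0.5 to 0.8 (5 to 37 with HC3). At 0.3 the gain is about 2 points with ordinary errors and slightly negative with HC3. For Kenya versus US the consequence is confounding of prior antibody with vaccine response, whose size the document does not allow one to compute. Overall impact is modest. The change is worth making because it is free, not because the trial's main conclusions depend on it.

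**What to change.** In section 10.4.3:

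1. Delete the dose-response purpose from this Part B document.
2. Name the contrasts: Group 3 versus Group 4 and, if the comparison in sections 2.1 and 10.1 is kept, Kenya 50 mcg versus US 50 mcg. Reconcile those sections with the synopsis objective, which asks for measurement only.
3. Analyse Group 3 versus Group 4 by ANCOVA of log10 Day 70 titre on log10 Day 0 titre, and report the adjusted geometric mean ratio with 95% CI.
4. Report fold rise from Day 0 by group beside the geometric means. Use fold rise for Kenya versus US and describe that comparison as non-randomised.
5. Optionally, specify unequal-variance or robust standard errors as a safeguard, accepting the few points of power that HC3 costs at this sample size.

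The cost is wording only. Day 0 serum is already drawn for ELISA, so no sample, visit or volunteer is added.

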# ADMINISTRATIVE MATTERS

To comply with Good Clinical Practice important administrative obligations relating to investigator responsibilities, monitoring, archiving data, audits, confidentiality and publications must be fulfilled. See Appendix B for details.

# Appendix A: World Medical Association Declaration of Helsinki

Recommendations guiding physicians

in biomedical research involving human subjects

Adopted by the 18th World Medical Assembly

Helsinki, Finland, June 1964

and amended by the

29th World Medical Assembly

Tokyo, Japan, October 1975

35th World Medical Assembly

Venice, Italy, October 1983

41st World Medical Assembly

Hong Kong, September 1989

and the

48th General Assembly

Somerset West, Republic of South Africa, October 1996

INTRODUCTION

It is the mission of the physician to safeguard the health of the people. His or her knowledge and conscience are dedicated to the fulfilment of this mission.

The Declaration of Geneva of the World Medical Association binds the physician with the words, "The health of my patient will be my first consideration," and the International Code of Medical Ethics declares that, "A physician shall act only in the patient's interest when providing medical care that might have the effect of weakening the physical and mental condition of the patient."

The purpose of biomedical research involving human subjects must be to improve diagnostic, therapeutic and prophylactic procedures and the understanding of the etiology and pathogenesis of disease.

In current medical practice most diagnostic, therapeutic or prophylactic procedures involve hazards. This applies especially to biomedical research.

Medical progress is based on research that ultimately must rest in part on experimentation involving human subjects.

In the field of biomedical research a fundamental distinction must be recognized between medical research in which the aim is essentially diagnostic or therapeutic for a patient, and medical research, the essential object of which is purely scientific and without implying direct diagnostic or therapeutic value to the person subjected to the research.

Special caution must be exercised in the conduct of research that may affect the environment, and the welfare of animals used for research must be respected.

Because it is essential that the results of laboratory experiments be applied to human beings to further scientific knowledge and to help suffering humanity, the World Medical Association has prepared the following recommendations as a guide to every physician in biomedical research involving human subjects. They should be kept under review in the future. It must be stressed that the standards as drafted are only a guide to physicians all over the world. Physicians are not relieved from criminal, civil and ethical responsibilities under the laws of their own countries.

I. BASIC PRINCIPLES

1. Biomedical research involving human subjects must conform to generally accepted scientific principles and should be based on adequately performed laboratory and animal experimentation and on a thorough knowledge of the scientific literature.
2. The design and performance of each experimental procedure involving human subjects should be clearly formulated in an experimental protocol that should be transmitted for consideration, comment and guidance to a specially appointed committee independent of the investigator and the sponsor provided that this independent committee is in conformity with the laws and regulations of the country in which the research experiment is performed.
3. Biomedical research involving human subjects should be conducted only by scientifically qualified persons and under the supervision of a clinically competent medical person. The responsibility for the human subject must always rest with a medically qualified person and never rest on the subject of research, even though the subject has given his or her consent.
4. Biomedical research involving human subjects cannot legitimately be carried out unless the importance of the objective is in proportion to the inherent risk to the subject.
5. Every biomedical research project involving human subjects should be preceded by careful assessment of predictable risks in comparison with foreseeable benefits to the subject or to others. Concern for the interests of the subject must always prevail over the interests of science and society.
6. The right of the research subject to safeguard his or her integrity must always be respected. Every precaution should be taken to respect the privacy of the subject and to minimize the impact of the study on the subject's physical and mental integrity and on the personality of the subject.
7. Physicians should abstain from engaging in research projects involving human subjects unless they are satisfied that the hazards involved are believed to be predictable. Physicians should cease any investigation if the hazards are found to outweigh the potential benefits.
8. In publication of the results of his or her research, the physician is obliged to preserve the accuracy of the results. Reports of experimentation not in accordance with the principles laid down in this Declaration should not be accepted for publication.
9. In any research on human beings, each potential subject must be adequately informed of the aims, methods, anticipated benefits and potential hazards of the study and the discomfort it may entail. He or she should be informed that he or she is at liberty to abstain from participation in the study and that he or she is free to withdraw his or her consent to participation at any time. The physician should then obtain the subject's freely‑given informed consent, preferably in writing.
10. When obtaining informed consent for the research project the physician should be particularly cautious if the subject is in a dependent relationship to him or her or may consent under duress. In that case the informed consent should be obtained by a physician who is not engaged in the investigation and who is completely independent of this official relationship.
11. In case of legal incompetence, informed consent should be obtained from the legal guardian in accordance with national legislation. Where physical or mental incapacity makes it impossible to obtain informed consent, or when the subject is a minor, permission from the responsible relative replaces that of the subject in accordance with national legislation.
12. Whenever the minor child is in fact able to give consent, the minor's consent must be obtained in addition to the consent of the minor's legal guardian.
13. The research protocol should always contain a statement of the ethical considerations involved and should indicate that the principles enunciated in the present Declaration are complied with.

II. MEDICAL RESEARCH COMBINED WITH PROFESSIONAL CARE
(Clinical research)

1. In the treatment of the sick person, the physician must be free to use a new diagnostic and therapeutic measure, if in his or her judgment it offers hope of saving life, re-establishing health or alleviating suffering.
2. The potential benefits, hazards and discomfort of a new method should be weighed against the advantages of the best current diagnostic and therapeutic methods.
3. In any medical study, every patient - including those of a control group, if any - should be assured of the best-proven diagnostic and therapeutic method. This does not exclude the use of inert placebo in studies where no proven diagnostic or therapeutic method exists.
4. The refusal of the patient to participate in a study must never interfere with the physician–patient relationship.
5. If the physician considers it essential not to obtain informed consent, the specific reasons for this proposal should be stated in the experimental protocol for transmission to the independent committee (I, 2).
6. The Physician can combine medical research with professional care, the objective being the acquisition of new medical knowledge, only to the extent that medical research is justified by its potential diagnostic or therapeutic value for the patient.

III. NON-THERAPEUTIC BIOMEDICAL RESEARCH INVOLVING HUMAN SUBJECTS (Non-clinical biomedical research)

1. In the purely scientific application of medical research carried out on a human being, it is the duty of the physician to remain the protector of the life and health of that person on whom biomedical research is being carried out.
2. The subjects should be volunteers ‑ either healthy persons or patients for whom the experimental design is not related to the patient's illness.
3. The investigator or the investigating team should discontinue the research if in his/her or their judgment it may, if continued, be harmful to the individual.
4. In research on man, the interest of science and society should never take precedence over considerations related to the well being of the subject.

# Appendix B: Administrative Matters

**I. Responsibilities of the Investigator IAW 21 CFR 312.60 and ICH E6, section 4**

- To ensure that he/she has sufficient time to conduct and complete the study and has adequate staff and appropriate facilities that are available for the duration of the study and to ensure that other studies do not divert essential subjects or facilities away from the study at hand.
- To submit an up-to-date curriculum vitae and other credentials (e.g. medical license number in the United States) to the sponsor and—where required—to relevant authorities.
- To acquire the normal ranges for laboratory tests performed locally and, if required by local regulations, obtain the Laboratory License orCertification.
- Additional laboratory assays may be performed on stored serum samples left over after protocol specified laboratory testing is completed. This may include clinical tests performed in the evaluation of a volunteer’s medical problem or additional malaria specific immunologic evaluations as they become available. In either case, the PI will inform the IRB of any non-protocol specified laboratory testing that may occur.
- To prepare and maintain adequate case histories designed to record observations and other data pertinent to the study.
- To conduct the study in compliance with the protocol and appendices.
- To cooperate with a representative of USAMMDA and GSK Biologicals in the monitoring process of the study and in resolution of queries about the data.

